## Abstract

**Introduction:**

*Staphylococcus aureus* bacteraemia (SAB) is a common and severe infection, with a 90-day mortality of 24%–32%. Cloxacillin is regarded as a first-line antibiotic treatment in SAB in Sweden. However, exposure to cloxacillin in real-world hospitalised patients with SAB, most of whom are elderly patients treated outside the intensive care unit, is not well described. There are also limited data on the role of unbound cloxacillin exposure in relation to renal function or drug-induced toxicity.

**Methods and analysis:**

This multicentre, prospective, observational clinical trial will include 95 adult patients with methicillin-susceptible *S. aureus* bacteraemia, treated with cloxacillin. Patients with endocarditis, polymicrobial bacteraemia or those considered unsuitable for cloxacillin treatment are excluded. Trough and peak total and unbound cloxacillin concentrations will be measured at steady state at days 2 and 7. Blood cultures will be obtained at days 2, 3, 4 and 7 to assess time to negative culture. Renal function will be assessed daily for plasma creatinine and at days 1 and 6 for cystatin C and for 12-hour urine creatinine clearance. In a novel approach to detecting nephrotoxicity, renal tubular damage biomarkers will be measured at days 1 and 6 (KIM-1, N-acetyl-β-D-glucosaminidase, neutrophil gelatinase-associated lipocalin, urine cystatin C, alpha-1-microglobulin). Detection of neurologic symptoms such as confusion, tremor, hallucinations and convulsions, as well as consciousness, will be monitored daily using a structured evaluation form.

We aim to investigate to which extent target attainment (100% of the dosing interval during which the free (unbound) drug concentration exceeds the minimum inhibitory concentration) is achieved with standard dosing of cloxacillin in a real-world cohort of hospitalised patients with SAB, and whether initial renal function can predict who is at risk for underdosing or overdosing. We will also explore whether neurological or renal damage is prevalent and associated with cloxacillin levels.

**Ethics and dissemination:**

Ethics approval has been granted by the Swedish Ethical Review Authority (EUCT 2023-505148-20-00) as part of a low-intervention clinical trial approval according to EU regulation 536/2014. Results will be disseminated in a peer-reviewed journal and at academic conferences.

**Trial registration number:**

EUCT 2023-505148-20-00.

STRENGTHS AND LIMITATIONS OF THIS STUDYInvestigating cloxacillin treatment in a real-world, elderly *Staphylococcus aureus* bacteraemia population.Measuring unbound cloxacillin concentrations and assessing renal toxicity with several established and novel markers.Due to a limited sample size, any association between concentration and toxicity should be considered exploratory.

## Introduction

### Background

*Staphylococcus aureus* bacteraemia (SAB) is a severe infection with a reported prevalence of 9.3–65 cases/100 000/year and a 30-day and 90-day mortality rate ranging from 14%–23% and 24%–32%, respectively.^1^,^3^ Isoxazolyl penicillins, such as cloxacillin, are considered a first-line therapy when treating methicillin-susceptible SAB.^4^ Standard dosage of intravenous cloxacillin for SAB varies depending on infection severity and local dosing recommendations.^5 6^ Currently, a dose of 2 g every 6–8 hours is recommended for SAB without endocarditis in Sweden.^7 8^

In general, beta-lactam antibiotics show a time-dependent efficacy, where an insufficient percentage of the dosing interval during which the unbound (free) antibiotic concentration remains above the minimum inhibitory concentration (MIC) (fT>MIC) increases the risk of clinical failure and resistance development.^9 10^ For severe infections, it is recommended that unbound (free) plasma concentration remains above the MIC of the pathogen during therapy (100% fT>MIC).^11^ Cloxacillin is highly protein bound, like other isoxazolyl penicillins (eg, dicloxacillin and flucloxacillin), with an unbound fraction of 6%–8% based on data from the manufacturer.^7 12^ There are limited data on whether recommended dosing of intermittently given cloxacillin is sufficient to reach the recommended target in real-world patients with SAB. Since flucloxacillin protein binding has shown a variability between 2% and 72% in critically ill patients,^13^ an individualisation of cloxacillin dosing may be warranted.

Most therapeutic drug monitoring studies of cloxacillin involve critically ill patients with SAB in the intensive care unit (ICU) or patients with infective endocarditis.^14^,^16^ However, the typical patient with SAB is older (66–75 years) without endocarditis and is treated outside of the ICU.^17^,^20^ In younger patients outside the ICU, a small study in which total concentrations were measured suggests a low probability of achieving 100% fT>MIC with intermittent cloxacillin dosing regimens.^21^ However, these results may not be applicable to an elderly population, among whom an increased prevalence of chronic kidney disease can be anticipated,^22^ since augmented renal clearance is a risk factor for insufficient exposure of beta-lactam antibiotics.^23^ Estimation of renal function has shown potential in identifying insufficient exposure among ICU patients for some low-to-medium protein bound beta-lactam antibiotics,^24^ but the relevance for highly protein bound antibiotics among patients with SAB outside of the ICU is unknown.

Acute kidney injury (AKI) is common for patients with SAB, with a reported incidence between 17% and 43%, and is associated with an increased 30-day mortality.^25^,^27^ Although AKI has been considered to be caused by the infection per se, treatment with isoxazolyl penicillins has also been associated with an increased risk of nephrotoxicity.^28^ There are limited data on whether the increased risk of isoxazolyl penicillin-induced AKI is concentration-dependent, but small studies suggest that about 57%–71% of patients with manifest AKI had a cloxacillin concentration above 50 mg/L.^29 30^ The reported median time of AKI recovery after cloxacillin cessation is 5 days, which implies that early detection of AKI is beneficial for timely dose adjustment.^29^ However, an increase of serum creatinine as a routine marker for kidney injury is rarely detected until 1–2 days after AKI onset. AKI onset usually occurs within days after therapy initiation,^29^ suggesting the development of acute tubular necrosis.^29 31^ Biomarkers of renal tubular injury may have the potential to detect AKI at an earlier stage than serum creatinine,^32^ but their diagnostic potential has not been widely evaluated in patients treated with beta-lactam antibiotics.^33^

Recent findings suggest that high concentrations of beta-lactam antibiotics may be associated with neurologic symptoms, including persistent coma and delirium, resulting in longer hospital stays.^16 34 35^ A small study reported that neurologic symptoms in critically ill patients improved for all patients after dose reduction of cloxacillin.^16^ It is therefore important to identify whether neurological symptoms may be associated with antibiotic concentration levels, including non-ICU patients with SAB. We plan to conduct a prospective observational study in a real-world, hospitalised population with SAB. The study is approved as a low-interventional clinical trial registered in CTIS (Trial registration number: EUCT 2023-505148-20-00).

We aim to investigate to which extent target attainment (100% fT>MIC) is achieved with standard dosing of cloxacillin in a real-world cohort of hospitalised patients with SAB, and whether initial renal function can predict who is at risk for underdosing or overdosing. Furthermore, we will explore whether renal- or neurotoxicity may be associated with unbound cloxacillin concentrations, including the potential for novel renal tubular damage biomarkers to identify beta-lactam induced AKI. Lastly, we will survey the trial participants’ experience of taking part in the trial.

## Methods and analysis 

### Trial design

The KLOX-SAB study is a multicentre, prospective, observational clinical trial investigating standard care treatment with cloxacillin for patients with SAB in southeast Sweden. The trial is registered as low-interventional and abides by Good Clinical Practice standards.^36^

### Trial population

The trial population will consist of adult patients with a blood culture with growth of *Staphylococcus aureus,* obtained no more than 72 hours prior to inclusion. The participant is treated with cloxacillin therapy started at the time of, or no more than 72 hours prior to, inclusion, and has given informed consent. Inclusion and exclusion criteria are found in table 1. Patients will be treated with standard-of-care according to the treating physician, normally intravenous cloxacillin 2 g every 6–8 hours for at least 7 days.

**Table 1 T1:** Inclusion and exclusion criteria

Inclusion criteria	Exclusion criteria
Positive blood culture with *Staphylococcus aureus* obtained no more than 72 hours before inclusion	*S. aureus* not susceptible (S) to cloxacillin
≥18 years of age	Polymicrobial bacteraemia or concomitant infection which demands treatment with an antibiotic with broader spectrum than cloxacillin.
Treatment with cloxacillin, started at inclusion or no more than 72 hours before inclusion	Endocarditis or other intracardial infections detected by echocardiography.
Informed oral and written consent	Serious allergic reaction to cloxacillin, other penicillins or cephalosporins.
	Any contraindication for cloxacillin treatment or trial participation as judged by the treating physician.
	Moribund; when a cure is not deemed achievable with active treatment and aim of care is to give end-of-life or best supportive care
	Breastfeeding and not able or willing to interrupt breastfeeding
	Unconsciousness, not willing to participate or assessed as having difficulties understanding the significance of trial participation due to mental disability or language barriers.
	Participation in a clinical trial 30 days prior to initiation
	Prior participation in the current trial

Cloxacillin susceptibility is assessed using clinical break-points from 2025 by the European Committee on Antimicrobial Susceptibility Testing (EUCAST).^5^

Participants with no available echocardiography at the time of inclusion may still be recruited. If endocarditis is detected with echocardiography later during the trial, the participant will be excluded.

### Recruitment strategy

Participants admitted to the University Hospital in Linköping, Vrinnevi Hospital in Norrköping or Kalmar County Hospital and who are deemed eligible will be recruited. The trial aims to recruit 95 patients. A clinical routine has been established at each site previous to the trial, where each positive SAB finding initiates an infectious specialist consultation, including bedside assessment when possible.

### Trial procedures

The trial duration for each participant will be 30 days. Initial blood and urine sampling will occur during the first 7 in-hospital days, and outcome data will be gathered on day 30 from the medical record (table 2).

Each positive blood culture will be reported to an infection specialist by direct contact from the microbiology lab at each site. Eligibility of trial participation will be assessed, where eligible patients are informed about and asked to participate in the trial by a doctor or nurse associated with the trial. After written informed consent is obtained, participant characteristics are registered (gender, age, weight, height). Comorbidity will be estimated using the Charlson comorbidity index.^37^ Infection severity will be estimated via the National Early Warning Score 2.^38^ Current medications and dosing at time of inclusion will be recorded as will any addition, withdrawal or dosing adjustments during the trial duration. Prevalence of neurologic symptoms will be registered with occurrence of tremor, hallucination, convulsions or confusion corresponding to ≥2 points measured by Nursing Delirium Screening Scale,^39^ as well as consciousness level assessed using the Reaction Level Scale-85.^40^ Blood cloxacillin concentrations will be sampled prior to administration (trough) as well as within 30 min after end of cloxacillin infusion (peak) (table 2). Additional measurements of plasma liver and renal biomarkers (alanine aminotransferase (ALT), cystatin C, creatinine and albumin) and blood cultures (aerobic+anaerobic) will be sampled at the same time as clinical sampling or trough level sampling.

**Table 2 T2:** Trial procedures

Procedures	Day							
	1	2	3	4	5	6	7	30 (28–35)
Inclusion/exclusion criteria eligibility	√							
Informed consent	√							
Demographic and clinical data, comorbidity, current medication, baseline symptoms CNS	√							
Neurological symptoms, NEWS-2, medication and dosing adjustments	√	√	√	√	√	√	√	
Plasma samples: ALT, cystatin C, albumin.	√					√		
Plasma creatinine, eGFR estimation	√	√	√	√	√	√	√	
Urine sample for renal damage marker measurement and initiation of 12 hours urine sampling for creatinine clearance measurement	√					√		
Plasma samples for cloxacillin-concentration measurement (peak and trough) and urine creatinine measurement with creatinine clearance calculation		√					√	
Blood culture		√	√	√			√	
Final diagnosis, duration of bacteraemia, mortality, complexity of infection								√
Serious adverse events (deaths)		√	√	√	√	√	√	√
End of trial								*√*

ALT, alanine aminotransferase; CNS, central nervous system; eGFR, estimated glomerular filtration rate; NEWS, National Early Warning Score.

Urine will be sampled for renal tubular damage biomarker measurements (cystatin C, kidney injury molecule 1 (KIM-1), N-acetyl-β-D-glucosaminidase (NAG), neutrophil gelatinase associated lipocalin (NGAL), alpha-1-microglobulin (A1M) and additional biomarkers associated with renal damage). A 12-hour urine collection will subsequently be initiated to measure creatinine clearance and total urine production (table 2). Total urine volume will be determined by weight and sampled for creatinine clearance analysis.

At the end of the trial participation, mortality, lost-to-follow-up, time to negative SAB blood culture, assessment of SAB complexity according to Infectious Diseases Society of America,^41^ and diagnosis codes will be collected from the medical record.

More details on the frequency of data and sample collection can be found in table 2.

### Selected cloxacillin PK/PD targets for efficacy and toxicity

Methicillin-susceptible *S. aureus* shows a cloxacillin MIC distribution epidemiological cut-off (ECOFF) breakpoint at 0.5 mg/L, based on wild-type distributions from the EUCAST.^42^ Thus, the exposure target in this trial is set to 100% fT>MIC_ECOFF_, maintaining an unbound concentration above 0.5 mg/L.^11^ Overexposure is defined as maintaining an unbound concentration above 5 mg/L (100% fT>10xMIC_ECOFF_) or a corresponding total concentration above 50 mg/L, which was found in >50% of patients with a manifest AKI.^29 30 43^ AKI will be assessed by the change of serum creatinine levels, as described in Kidney Disease: Improving Global Outcomes (KDIGO) criteria.^44^ Neurological symptoms such as persistent coma and delirium have been associated with increased total trough cloxacillin concentrations with a lower range of 100 mg/L.^16^

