### Endpoints

Primary endpoints:

Proportion of patients with SAB reaching 100% ƒT>MIC_ECOFF_, that is, an unbound cloxacillin trough level of >0.5 mg/L at days 2 and 7 and its association with renal function.Proportion of patients with SAB reaching an unbound cloxacillin trough level of >5 mg/L or total trough level of >50 mg/L at days 2 and 7 and its association with renal function.

Secondary endpoints:

Prevalence of increased levels of urine markers for renal tubular damage (cystatin C, KIM-1, NAG, NGAL, A1M) compared with reference values, and its association with cloxacillin concentrations (peak and trough) at days 2 and 7.Prevalence of AKI based on creatinine, defined by KDIGO, measured daily between days 1 and 7.Onset of new symptoms from the central nervous system (ie, decreased consciousness, seizures, tremor, hallucinations or confusion), with day 1 regarded as baseline, measured daily on days 1–7, in relation to cloxacillin concentrations (peak and trough) at days 2 and 7.Descriptive characteristics of the SAB population, including sex, age, weight, comorbidity, medications, infection severity, complexity, duration and 30-day mortality.Levels of additional exploratory biomarkers in urine and plasma associated with nephrotoxicity or neurotoxicity.The trial participants’ experience taking part in the trial.

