### Hypothesis and sample size calculations

In this low-interventional clinical trial, sample size calculation is primarily needed for the analyses in relation to renal function.

We have previously shown that an eGFR cut-off of approximately 45 mL/min/1.73 m^2^ may be used to predict sufficient exposure in a study on beta-lactam antibiotic treatment within a population of patients in ICUs.^24^ We hypothesised that cloxacillin exposure is similar to other beta-lactam antibiotics when related to renal function. Cut-offs were selected from chronic kidney disease stages according to clinical applicability as well as superiority in sensitivity and specificity in detecting insufficient exposure for other beta-lactam antibiotics.^24^

Based on the literature and our own unpublished clinical data (median age for patients with SAB in Region Östergötland is 72 years), we hypothesised that the proportion with eGFR <45 mL/min/1.73 m^2^ in the trial population (including individuals with HD, estimated ratio 10%) will be approximately 35%–40%.^22 47^

Furthermore, we hypothesise that 90% of individuals with eGFR ≤45 mL/min/1.73 m^2^ will reach the target of 100% ƒT>MIC_ECOFF_ (ie, a trough unbound concentration of cloxacillin >0.5 mg/L). This assumption was based on a limited number of previous studies where total cloxacillin concentrations were measured and related to eGFR.^15 16^ Based on the same studies, we hypothesised that 50% of individuals with eGFR ≤45 mL/min/1.73 m^2^ will reach tentatively toxic trough concentrations (ie, total concentration >50 mg/L, or unbound concentration >5 mg/L). For patients≥45 mL/min/1.73 m^2^, we hypothesise that 50% will reach an unbound concentration of at least 0.5 mg/L and for patients >60 mL/min/1.73 m^2^, 20% will have >5 mg/L.^16^

To ensure sufficient sample size in each renal function group, we estimated that 38 individuals with eGFR ≤45 mL/min/1.73 m^2^ and 57 patients with eGFR above 45 mL/min/1.73 m^2^ are required to detect a difference in predefined exposure cut-offs between renal groups, with a power of 0.8 and alpha value of 0.05. Consequently, at least 95 individuals will need to be included.

If participants decide to withdraw prematurely before day 4, a new participant will be recruited. Data collected prior to the withdrawal will be used in the analysis.

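### The two overexposure limits in the second primary endpoint (unbound 5 mg/L, total 50 mg/L) match only at a 10% unbound fraction, but the protocol gives 6%–8%

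*Protocol article*

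**What the plan says.** The section on PK/PD targets sets the ECOFF at 0.5 mg/L ("epidemiological cut-off (ECOFF) breakpoint at 0.5 mg/L") and then defines overexposure: "Overexposure is defined as maintaining an unbound concentration above 5 mg/L (100% fT>10xMIC_ECOFF_) or a corresponding total concentration above 50 mg/L". The Endpoints section carries the rule into the second primary endpoint, the proportion of patients "reaching an unbound cloxacillin trough level of >5 mg/L or total trough level of >50 mg/L" on days 2 and 7, together with its association with renal function.

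Background describes cloxacillin as highly protein bound, "with an unbound fraction of 6%–8% based on data from the manufacturer". It gives no other unbound fraction for this drug. It adds that "flucloxacillin protein binding has shown a variability between 2% and 72% in critically ill patients", which concerns a related drug in a different population.

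The total limit also has a basis of its own. Background reports that "about 57%–71% of patients with manifest AKI had a cloxacillin concentration above 50 mg/L", and the targets section refers to the same kind of data.

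In the sample size section, the 50% assumed for eGFR ≤45 is the share that "will reach tentatively toxic trough concentrations (ie, total concentration >50 mg/L, or unbound concentration >5 mg/L". The 20% assumed for eGFR >60 names only the 5 mg/L limit.

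**The concern.** The word *corresponding* tells the reader that the two limits express one exposure level on two scales, and the bracketed 10xMIC label then seems to apply to both. If they are not equivalent, the *or* rule does not measure what the label says. The lower hurdle decides each patient's status, and which hurdle is lower depends on that patient's protein binding.

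This affects a primary endpoint. The reported proportion would be taken as the share of patients whose unbound concentration stays above ten times the MIC throughout the dosing interval. In fact it could include many patients well below that level. The article's rationale stresses how little is known about unbound cloxacillin exposure, so the distinction matters.

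**Working it through.** **Inputs.** ECOFF 0.5 mg/L, unbound limit 5 mg/L and total limit 50 mg/L (PK/PD targets section); unbound fraction *f* of 6%–8% (Background).

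**Relation.** Unbound = *f* × total.

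**The plan's own figures.** 10 × 0.5 = 5 mg/L, so the unbound limit reproduces. The total said to correspond is 5/*f*. This equals 50 only when *f* = 5/50 = 10%, so the stated 50 mg/L does not reproduce at 6%–8%.

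| *f* | Unbound at total 50 mg/L | Multiple of ECOFF | Total at unbound 5 mg/L |
|---|---|---|---|
| 6% | 50 × 0.06 = 3.0 | 6 | 5/0.06 = 83.3 |
| 7% | 50 × 0.07 = 3.5 | 7 | 5/0.07 = 71.4 |
| 8% | 50 × 0.08 = 4.0 | 8 | 5/0.08 = 62.5 |
| 10% | 50 × 0.10 = 5.0 | 10 | 5/0.10 = 50.0 |

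**What the *or* rule does.** A patient is positive when total > 50 or *f* × total > 5, that is, when total exceeds the smaller of 50 and 5/*f*.

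- If *f* < 10%, then 5/*f* > 50. Unbound > 5 implies total > 50, so the composite equals total > 50 and the unbound limit adds nobody.
- If *f* > 10%, then 5/*f* < 50. The composite equals unbound > 5, and a patient can qualify without reaching total 50.

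Example: a total of 55 mg/L at 6%–8% is an unbound 55 × 0.06 = 3.3 to 55 × 0.08 = 4.4 mg/L. This patient counts as overexposed without meeting the 10xMIC criterion.

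**Illustration under assumptions.** The article gives no distribution of troughs. Assume log-normal total troughs with log-SD 1 and a median of 20 or 50 mg/L.

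- *f* uniform on 6%–8%: the composite rate is 18.0% (median 20) or 50.0% (median 50), identical to the total limit alone. The unbound limit alone gives 10.2% or 36.1%.
- *f* log-normal around 7% with geometric SD 1.5 to 2: the unbound limit alone supplies about 7%–20% of positives (median 20) or 3%–9% (median 50).

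These percentages show the mechanism. They are not predictions for this trial.

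**Sample size.** 50% against 20%, allocation 1.5, two-sided 0.05, power 0.80 with continuity correction gives 37 + 56 = 93, close to the stated 38 + 57 = 95. The calculation reproduces from its own inputs.

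**The case against.** The strongest defence is that 50 mg/L was not derived from 5 mg/L. It rests on the AKI data, and catching either a high total or a high unbound concentration is a reasonable choice for a drug whose binding is uncertain. The 6%–8% is a manufacturer's figure and real patients may differ. All of this stands as support for having two limits, and for saying that the total limit does not decide every patient. It does not make the limits correspond. An independent basis for 50 mg/L is a reason to report it as a measure in its own right.

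A reader might infer three stronger points that the documents do not support.

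- *Power is lost.* This requires the 20% planning rate to be purely unbound, so that the composite rate in the comparison group is higher. But the sample size section bases its assumptions on earlier studies that measured total concentrations, and the 20% may be shorthand for the composite in the preceding sentence. The spread of trough concentrations is not given either, so any power figure would be illustrative only.
- *The renal association is distorted because binding varies with albumin or renal function.* The article nowhere says that the cloxacillin unbound fraction depends on either.
- *Unbound >5 mg/L must be the only primary limit.* The aim concerning overdosing is not restricted to unbound concentration, and the total limit is the one with a stated AKI figure. Which limit is clinically right is not a matter for this point.

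**Conclusion.** The point holds as an incorrect equivalence within a primary endpoint threshold. On the article's own 6%–8%, the total limit sits at 60%–80% of the unbound limit (3.0–4.0 against 5 mg/L). For every patient below 10% unbound, the composite is simply total >50 mg/L and cannot be interpreted as 100% fT>10xMIC. Above 10% the unbound limit governs. This conclusion needs only the mass balance and the stated fraction. How many patients fall on each side of 10% is unknown until the trial's own data are seen.

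Severity is moderate. The *or* rule still classifies every patient with both measurements, the data collected are sufficient, and the sample size is not shown to be wrong. What fails is the meaning attached to the reported proportion, and the clarity about which definition each planning rate refers to.

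**What to change.** 1. Delete *corresponding* from the overexposure definition, or reconcile the two limits with the stated unbound fraction. Attach the 10xMIC label to the unbound limit only.
2. Report the proportion and the renal-function association separately for unbound >5 mg/L and total >50 mg/L, with a cross-table of the two on days 2 and 7.
3. State before the final analysis which definition is primary: the composite, the total limit or the unbound limit.
4. In the sample size section, say explicitly that the 50% and 20% rates refer to that same definition.

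The cost is a wording change and slightly more reporting, since the Sample analysis section already provides for total and free concentrations. The unbound-only proportion can be no higher than the composite. If a single limit is made primary and the planning rates turn out to be composite rates, those rates and the power should be rechecked.
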